### Randomization and blinding

This is a single-blind study. To ensure random allocation, serial numbers from 1 to 266 will be placed in sealed opaque envelopes for the patients. Specifically, numbers 1–38 will correspond to the preoperative TEAS group, numbers 39–76 will be assigned to the intraoperative TEAS group, numbers 77–114 will belong to the postoperative TEAS group, numbers 115–152 will be designated for the pre- and postoperative TEAS group, numbers 153–190 will be allocated to the perioperative TEAS group, numbers 191–228 will be assigned to the sham TEAS group, and numbers 229–266 will be assigned to the control group. The randomization process will be conducted by a study administrator who is not directly involved in the study.

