### Patient population and setting

The equation for sample size calculation, *n* = (Z*
_α/2_
* + Z*
_β_
*)^2^ × 2*σ*^2^/δ^2^ where σ represents the average score of the Mini-Mental State Examination (MMSE) evaluated on the third day after the operation between the two groups. Based on previous pre-experimental data, this study employs a two-sided test with *α* = 0.05 and a test efficiency of (1-β) = 0.9, resulting in Z_α/2_ = 1.96, Z_β_ = 1.282. *σ* denotes the standard deviation, while *δ* represents the mean difference of MMSE scores on the third day after the operation between the intervention and control groups. According to the pre-experiment results, σ is 2.35, δ is 2.0, and considering a 30% increase in the sample size, each group requires 38 patients. Therefore, a total of 266 patients will be sequentially enrolled after meeting the eligibility criteria, with the attending doctor informing each patient and obtaining their informed consent. This study adheres to the principles of the Declaration of Helsinki.

To expand our pool of research subjects, we will promote recruitment on the hospital’s official account. Throughout the intervention, patients will retain the final decision-making authority regarding their participation in the trial.

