### Data collection and management

Throughout the study, participants will be referred to by their participant numbers rather than by their names. Additionally, all relevant documents and files will be archived for a period of 5 years and will only be accessible to investigators who have signed a confidentiality agreement or to institutional or governmental auditors during the study. Data collection and management will be monitored by the Institutional Ethics Committee of Subei People’s Hospital, Jiangsu Province.

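### The printed allocation scheme ties serial numbers to arms in seven consecutive runs of 38 and states no step that makes the order random

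*Protocol article*

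**What the plan says.** Three sections of the protocol article bear on this.

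- **Randomization and blinding** states the aim and the device: "To ensure random allocation, serial numbers from 1 to 266 will be placed in sealed opaque envelopes for the patients". It then gives the arm for each number. The first two runs are "numbers 1–38 will correspond to the preoperative TEAS group, numbers 39–76 will be assigned to the intraoperative TEAS group". The next are "numbers 77–114 will belong to the postoperative TEAS group, numbers 115–152 will be designated for the pre- and postoperative TEAS group", then "numbers 153–190 will be allocated to the perioperative TEAS group, numbers 191–228 will be assigned to the sham TEAS group", and last "numbers 229–266 will be assigned to the control group". On who does it: "The randomization process will be conducted by a study administrator who is not directly involved in the study". The section calls the trial single-blind without saying who is blinded.
- **Patient population and setting** says that "a total of 266 patients will be sequentially enrolled after meeting the eligibility criteria", with the attending doctor informing patients and obtaining consent.
- **Data collection and management** says that "participants will be referred to by their participant numbers rather than by their names". It does not say whether these are the serial numbers of the randomisation section.

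The Design section places the conduct of the trial in January to December 2025. It gives no separate accrual period.

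**The concern.** A randomised allocation needs a random element somewhere: in the list, in the order of the envelopes, or in a draw. The article names the purpose, the container and the person in charge, but not that element. What it does fix is a non-random map from number to arm.

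Two things are at stake, depending on how the envelopes are used.

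1. **Used in number order.** The first 38 patients all get one arm, the next 38 another, and the controls come last. Any change over the enrolment period in case mix, surgical or anaesthetic practice, or assessor habits becomes a difference between arms. The doctor obtaining consent could foresee the next assignment and, knowingly or not, select patients for it.
2. **Shuffled or drawn at random.** Neither problem arises. The map still matters if the number drawn is also the number written on the patient's records, because the arm can then be looked up in the published article. The primary outcome rests on tests given by an examiner, and the control arm has no device while the stimulation schedules differ. Participant blinding therefore cannot cover all seven arms, and keeping assessors unaware of the arm would be worth protecting.

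**Working it through.** **The plan's own figure.** Inputs from Patient population and setting: Z values 1.96 and 1.282, σ = 2.35, δ = 2.0, 30% increase.

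- n = (1.96 + 1.282)² × 2 × 2.35² / 2.0² = 29.02 per group
- 29.02 × 1.3 = 37.73, rounded up to 38; 7 × 38 = 266

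The stated 38 and 266 reproduce. The seven printed ranges each hold 38 numbers and sum to 266, with no gap or overlap. The arithmetic of the scheme is sound; the question is only the order of use.

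**Foreseeability.** There are 265 steps from one allocation to the next.

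- In number order, each run has 37 repeats: 7 × 37 = 259, and 259/265 = 97.7%.
- Under a random permutation of the same 266 allocations, the chance that the next equals the previous is 37/265 = 14.0%.

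**Calendar windows, number order, even accrual (accrual period assumed).**

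| Assumed accrual | Patients per month | Time to fill one arm |
|---|---|---|
| 12 months | 266/12 = 22.2 | 38/22.2 = 1.71 months, about 7.4 weeks |
| 6 months (6-month follow-up must also fit inside 2025) | 266/6 = 44.3 | 38/44.3 = 0.86 months, about 3.7 weeks |

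Over 12 months the preoperative arm would be enrolled on about days 1–52 and the controls on about days 314–365. The centres of these two runs lie 6/7 of the accrual period apart, which is 10.3 months of 12.

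**What a time trend would do.** The documents give no figure for drift, so a range is assumed: a linear change of D points on the Mini-Mental State Examination (MMSE) over accrual. The bias in preoperative versus control is then D × 6/7. False-positive rates for the seven-group ANOVA come from a simulation with SD 2.35, no treatment effect and 3,000 runs per setting.

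| Assumed drift D (points) | Bias, number order | ANOVA false positives, number order | Same, random permutation |
|---|---|---|---|
| 0 | 0 | 5.0% | 4.7% |
| 0.5 | 0.43 | 8.7% | 5.7% |
| 1 | 0.86 | 25% | 5.3% |
| 2 | 1.71 | 85% | 5.0% |

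The biases compare with a design difference of 2.0 points. They depend on the total drift over accrual, not on whether accrual takes 6 or 12 months.

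**Disclosure.** This needs no arithmetic. The randomisation section speaks of serial numbers and the data section of participant numbers, and no sentence equates them. The serial numbers are described as being for the patients and no other number is mentioned, so identity is the natural reading, but it is an inference. If they are the same, the number gives the arm with certainty; if separate IDs are used, this part falls away.

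**The case against.** The best defence is that the scheme describes a drawing of lots. The section opens by declaring random allocation as its purpose, puts the numbers inside opaque envelopes, and hands the process to someone outside the study. Sealing a number makes most sense if nobody knows which will come out, and a fixed number-to-arm map is normal for lots. Sequential enrolment describes how patients enter, not the order in which envelopes are opened. An article may also leave the mechanics of sequence generation to the full protocol.

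Most of this stands. A random draw is plausible, and under it allocation is valid with exactly 38 per arm. What does not stand is the appeal to condensed format. The article does not merely omit detail: it prints a specific scheme which, followed literally in number order, is deterministic.

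Three stronger readings are tempting, and the documents do not support them:

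- **That the trial is not randomised.** The text shows that no random step is stated, not that none will be taken.
- **That the participant number discloses the arm for all 266 patients however the envelopes are used.** This requires the two kinds of number to be the same, which is not stated.
- **That a promised assessor blinding is broken.** The article says only single-blind. The one masking measure it describes concerns participants in the sham arm. Nothing says that cognitive assessors or laboratory staff are blinded, so what may be lost is a desirable safeguard rather than a declared one.

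**Conclusion.** The concern holds in conditional form. The allocation rule is badly fixed: the arm of every serial number is set in consecutive runs and no step makes the order random.

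- **If used in number order**, arm is fully confounded with calendar time and 97.7% of allocations repeat the one before. The window per arm is about 7.4 or 3.7 weeks, depending on the assumed accrual period. Because the arms would not overlap in time, any later adjustment for time would lean on an assumed shape for the trend. The bias and error rates above hold only for the assumed drifts.
- **If shuffled or drawn at random**, there is no calendar confounding. What remains is possible disclosure of the arm, and only if the serial number doubles as the participant number.

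Which case applies cannot be settled from the article. Every comparison in the trial rests on this step and the correction is cheap, so it should be made before enrolment. The sample size is not affected.

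**What to change.** - Have the independent administrator generate a computer random sequence of the 7 × 38 allocations. A full random permutation suffices. Permuted blocks of randomly varied size (for example 7 and 14) are an alternative: they keep the arms level over time but are easier to guess near block ends for staff who can see the schedules.
- Number the envelopes in enrolment order and put the arm inside. Delete the fixed number-to-arm ranges from the text.
- Use study IDs that do not encode the arm, and say so.
- Keep the list from the enrolling doctors, the cognitive assessors, the data collectors and the laboratory. State who is blinded.
- If enrolment has begun, document the method actually used: the order in which envelopes were opened, whether they were shuffled or drawn, and whether the serial number appears on records.

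The cost is a short script and a protocol amendment. No extra patients or staff are needed.

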### Patient and public involvement

Patients or members of the public were not involved in the design, conduct, reporting, or dissemination of this research. However, study participants will have access to the study results through our social media channels.

### Intervention

The control group will receive standard perioperative care, which includes preoperative health education, an optimized anesthesia plan, intraoperative heat preservation measures, and minimized surgical trauma.

The intervention groups and the sham intervention group will undergo transcutaneous electrical acupoint stimulation (TEAS) in addition to the standard perioperative care provided to the control group. Specifically, electrodes will be attached to the skin surface of the acupoint and connected to the transcutaneous electrical stimulators (SDZ-III, Suzhou Medical Technology, Suzhou, China). The device will operate at a frequency of 2/100 Hz, utilizing disperse-dense waveforms. The stimulation intensity will be adjusted to a level that the patient can tolerate, but will not exceed 10 mA. The output will consist of an asymmetrical biphasic pulse wave, with a pulse width of 0.2 ms ± 30% (based on electromagnetic compatibility basic performance testing).

Considering the specificities of gastrointestinal organs and the principles of “Xingnao Kaiqiao Acupuncture” in traditional Chinese medicine (22), two acupuncture points have been selected: bilateral Neiguan (PC6) and Zusanli (ST36). Traditional Chinese medicine posits that gastrointestinal surgeries, like those causing physical trauma, may lead to essence deficiency, loss of “Qi, “stagnation, and blood stasis. Therefore, postoperative recovery should focus on eliminating blood stasis, promoting collateral circulation, and restoring visceral “Qi” (23).

PC6 is located on the inner side of the forearm, approximately 3 cm proximal to the transverse carpal crease, positioned between the palmaris longus tendon and the radial flexor carpi tendon (24). PC6 is an acupoint on the Pericardium Meridian of Hand Jueyin and is closely related to mental activities, cognitive function, and brain function (25). ST36 is located 3 inches below the outer side of the knee (26). ST36 is considered one of the primary acupoints on the Stomach Meridian of Foot Yangming and is associated with functions such as regulating the spleen and stomach, tonifying the middle, replenishing Qi, and promoting meridian flow (27). Please refer to Figure 2 for the precise location of these acupoints. During TEAS treatment, the acupoints on the same side will be grouped together for stimulation.

**Figure 2 fig2:**
[figure not shown]
Location of acupoints.

The timing of TEAS treatments for each group were as follows:Preoperative TEAS group: 30 min before anesthesia (28).Intraoperative TEAS group: From 30 min before anesthesia to the end of surgery (29).Postoperative TEAS group: For 7 consecutive days after the operation, once daily in the morning, with each session lasting 30 min (30).Pre-and postoperative TEAS group: From 1 day before the operation until 7 days after, once daily in the morning, with each session lasting 30 min (30).Perioperative TEAS group: 30 min before anesthesia until the end of surgery, 1 day before the operation, and on the 1st, 2nd, and 3rd days after surgery in the morning, each session lasting 30 min (14).Sham TEAS group: Electrodes will be placed in the same manner as the perioperative TEAS group but without electrical stimulation. Participants will be informed that the treatment has no sensation.

Two nursing postgraduates, who will serve as interveners, are required to spend 2 months in the Traditional Chinese Medicine Department of the hospital, dedicating 4 h each day to learning the functions and locations of acupoints, as well as the inspection and use of the instruments. To be eligible to participate in this intervention, the interveners must successfully pass a final examination, which will assess both theoretical knowledge and practical skills, administered by the Traditional Chinese Medicine Department.

During the experiment, a specialist from the Chinese Medicine Department will be invited to assess the appropriateness of acupoint selection and treatment intensity on a weekly basis. If any inaccuracies are identified in either the acupoint selection or treatment intensity, the intervener will be required to rejoin the Traditional Chinese Medicine Department for further training until they can accurately locate the acupoints and determine the correct treatment intensity. If a patient is affected by any such inaccuracies, they will be required to withdraw from the study.

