TEAS treatments administered at various times have demonstrated improvements in postoperative cognition. However, it is important to note that long-term electroacupuncture treatment may lead to the development of a ‘tolerance effect,’ which triggers a negative feedback mechanism and reduces the number of receptors, potentially diminishing its therapeutic efficacy (19). Therefore, this study aims to outline the protocol for a research project currently in the planning stage, designed to determine the optimal timing of TEAS for enhancing postoperative recovery in elderly patients.

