## Discussion

Research has shown that the timing of TEAS interventions—whether administered 10–30 min preoperatively, throughout the entire surgical procedure, or solely preoperatively versus a combination of preoperative and postoperative treatment—can significantly improve cognitive function (12–14). Extended use of TEAS may lead to a “tolerance effect,” potentially diminishing its efficacy over time (19). Consequently, this protocol aims to investigate the optimal timing for TEAS to improve postoperative recovery in elderly patients. The results are expected to assist clinicians in formulating more effective perioperative management strategies, reducing the incidence of POCD, and enhancing postoperative cognitive function and quality of life for elderly patients.

Additionally, given the potential for a “tolerance effect” associated with prolonged TEAS use, it is essential to examine how varying intervention durations at different timings might influence this phenomenon. Future research should evaluate the impact of different intervention durations at these timings to ensure the sustained efficacy and safety of TEAS. Furthermore, exploring the effects of TEAS across diverse surgical procedures and patient subgroups will contribute to validating its generalizability and applicability. Further studies are needed to confirm the long-term effects and safety of TEAS to establish its reliability in clinical practice.

This study has several notable strengths. Firstly, it is the pioneering investigation into the effects of different TEAS timings on the postoperative recovery of elderly patients with gastrointestinal tumors, as previously mentioned. Second, we assessed the long-term cognitive function. Many studies have discussed TEAS in the short term, for example, in the third and seventh days after the operation (32, 45). However, POCD can last for months or years, and we investigated the cognitive function of patients 1, 3, and 6 months postoperative (6).

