Furthermore, some studies have explored the impact of TEAS on factors such as exhaustion, defecation, eating, and the time taken to get out of bed for the first time, as well as perioperative Numeric Rating Scale (NRS) scores. However, limited research has focused on determining the most suitable timing for TEAS to enhance the postoperative recovery of patients. Therefore, this study is expected to suggest an optimal time window for expediting the recovery of patients with gastrointestinal tumors.

It is important to acknowledge certain limitations in this protocol. Due to the low outpatient follow-up rate observed in previous investigations, we were limited to using the TICS-m scale to assess long-term cognitive function post-operation, which differs from the previous neuropsychological tests. This limitation may introduce some bias, as it only allows for the detection of cognitive impairment without the ability to directly compare long-term cognitive function before and after the operation. Furthermore, as this is a single-center study, the results may not be fully generalizable to other research centers or populations, limiting the external validity of our findings. To address these limitations, future studies should consider multi-center designs to increase the diversity of the patient sample and enhance the applicability of the results across different settings. Additionally, expanding the range of neuropsychological assessments used to evaluate cognitive function, along with incorporating multiple testing points in longitudinal studies, would provide a more comprehensive and nuanced understanding of cognitive changes post-operation. These improvements would contribute to refining the research design and furthering our understanding of cognitive recovery in this context.

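### The five TEAS arms differ in amount of stimulation as well as in timing, so a better result in one arm cannot be read as the optimal timing

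*Protocol article*

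**What the plan says.** The Introduction describes the project as "designed to determine the optimal timing of TEAS for enhancing postoperative recovery in elderly patients". The Abstract words its purpose the same way, and the Discussion says that "this study is expected to suggest an optimal time window for expediting the recovery of patients with gastrointestinal tumors".

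The Intervention section gives all active arms the same acupoints, frequency, waveform and 10 mA ceiling. The five schedules, listed after Figure 2, are:

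- Preoperative: "Preoperative TEAS group: 30 min before anesthesia".
- Intraoperative: "From 30 min before anesthesia to the end of surgery".
- Postoperative: "For 7 consecutive days after the operation, once daily in the morning, with each session lasting 30 min".
- Pre- and postoperative: "From 1 day before the operation until 7 days after, once daily in the morning, with each session lasting 30 min".
- Perioperative: "30 min before anesthesia until the end of surgery, 1 day before the operation, and on the 1st, 2nd, and 3rd days after surgery", with the daily sessions lasting 30 min.

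Under Main outcome, the neuropsychological battery is given before surgery and on day 3, and TICS-m at 1, 3 and 6 months. The sample size rests on day-3 MMSE. Statistical analysis describes ANOVA or Kruskal-Wallis across the groups.

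On duration, the Discussion says: "Future research should evaluate the impact of different intervention durations at these timings". It does not say that duration already varies across the present arms.

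**The concern.** With the device settings held constant, two things still change from arm to arm: when stimulation is given and how much is given. A comparison of arm means cannot tell them apart. If benefit builds up with minutes, a long regimen does best and would be reported as the best time window. If prolonged stimulation loses effect, as the tolerance argument in the Introduction and Discussion suggests, long regimens do worse and a short one would be credited for its timing. The attribution to timing is the trial's headline conclusion, so the wording of that conclusion is what is at stake.

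**Working it through.** **The plan's own figure.** (1.96 + 1.282)² × 2 × 2.35² / 2.0² = 29.02. Then 29.02 × 1.3 = 37.73, rounded up to 38, and 7 × 38 = 266. The sample size reproduces and is not affected by this point.

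**Total minutes per arm.** S is the time in minutes from start of anesthesia to end of surgery. The article gives no value, so 120 to 300 is an assumption.

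| Arm | Formula | S=120 | S=180 | S=240 | S=300 |
|---|---|---|---|---|---|
| Preoperative | 30, if read as a duration | 30 | 30 | 30 | 30 |
| Intraoperative | 30 + S | 150 | 210 | 270 | 330 |
| Postoperative | 7 × 30 | 210 | 210 | 210 | 210 |
| Pre- and postoperative | 8 × 30, or 9 × 30 if the day of surgery counts | 240 or 270 | 240 or 270 | 240 or 270 | 240 or 270 |
| Perioperative | (30 + S) + 30 + 3 × 30 = 150 + S | 270 | 330 | 390 | 450 |

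The figures 30, 210 and 240 need no assumption on S: 240 / 30 = 8-fold. Some arms may coincide at a particular S (intraoperative and postoperative at S = 180), but that would be chance, not design.

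**Minutes by the day-3 battery.** The ranges reflect whether the day-3 session precedes the test and, for the pre- and postoperative arm, whether the day of surgery counts.

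- Preoperative: 30
- Intraoperative: 30 + S
- Postoperative: 60 to 90
- Pre- and postoperative: 90 to 150
- Perioperative: 120 + S to 150 + S

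The two 7-day arms have had at most 3 of their 7 postoperative sessions by then. The perioperative arm has had all of its schedule, or all but one session.

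**Illustration of the consequence.** Suppose timing has no effect and day-3 MMSE rises only with minutes delivered. Take SD 2.35, 38 per arm, the day-3 minutes above (no day-of-surgery session in the pre- and postoperative arm) and zero minutes in the sham and control arms. The slopes are hypothetical and have no source in the article.

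| Slope per 100 min | S | Seven-arm ANOVA significant | Perioperative arm has the highest mean of the five |
|---|---|---|---|
| 0.5 points | 120 to 240 | 52% to 96% | 74% to 86% |
| 0.25 points | 120 to 240 | 14% to 37% | 49% to 64% |

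Five equally effective arms would each come first in 20% of trials. A declining dose response would push the other way.

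**What the nested pairs can show.**

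- Intraoperative minus preoperative adds S min.
- Pre- and postoperative minus postoperative adds 30 min (60 if the day of surgery counts).
- Perioperative minus intraoperative adds 30 + 90 = 120 min.

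Each pair adds a period and minutes at once. The standard error of a pairwise difference is 2.35 × √(2/38) = 0.54 MMSE points. A difference of 0.9 points (0.5 per 100 min × 180 min) has about 38% power at two-sided 0.05. Power of 80% needs about (1.96 + 0.84) × 0.54 = 1.5 points.

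**The case against.** The best defence is that this is a pragmatic comparison of regimens. The Abstract speaks of timing strategies, each schedule carries its own literature reference, the Discussion names duration as an open question, and the closing claim is only that the trial is expected to suggest a window. This stands as a defence of the design: comparing packages is legitimate and no arm needs to change. It does not rescue the wording, because the Introduction and Discussion promise a timing answer, and no later analysis plan can recover a factor that the design does not separate.

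Four stronger readings are tempting, and the article does not support them.

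- A reader might put one fixed figure, such as 390 min, on the longest arm. That needs S = 240, which the article does not give.
- A reader might infer that the longest regimen is bound to win. That assumes accumulating benefit, while the article itself raises tolerance, which acts in the opposite direction.
- A reader might infer that the 7-day regimens are never assessed as written. That is true only of the day-3 battery. TICS-m at 1, 3 and 6 months is also in the primary outcome and follows completed courses.
- A reader might hope that the nested contrasts, or a model with minutes as a covariate, would isolate timing. The contrasts add minutes along with a period. Planned minutes are constant within three arms and vary in the other two only with S, so a minutes term would draw largely on surgery length, which may itself affect cognition.

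**Conclusion.** The point holds for the claim, not for the design. Timing and total stimulation vary together across the five arms, by at least 8-fold in minutes on the article's own text, if the preoperative entry is a 30-min duration. Under an assumed S of 120 to 300 min, the perioperative-to-preoperative ratio is 9 to 15 (270/30 to 450/30). The trial can say which regimen did better, but not that its timing was the reason. The bias could favour long or short regimens, so no direction is claimed, and the percentages above illustrate one hypothetical dose response only. The article describes no formal ranking of arms. Selection of a best arm is implied by the stated aim of finding an optimum.

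**What to change.** Leave all regimens unchanged and make these edits:

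1. In the Abstract (Purpose and Discussion), the Introduction and the Discussion, restate the objective and expected conclusion as a comparison of five TEAS regimens that differ in timing and in amount.
2. Name three contrasts: intraoperative minus preoperative, pre- and postoperative minus postoperative, and perioperative minus intraoperative. Read each only as the effect of adding stimulation in that period, and state its limited power (standard error about 0.54 MMSE points).
3. Report minutes delivered per arm, by day 3 and in total.
4. Where the Discussion defers duration to future work, add that duration already differs across these arms.
5. Clarify whether the pre- and postoperative schedule includes the day of surgery, and whether the preoperative entry is a duration or a start time. The minutes and the contrasts depend on both.

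Do not add a minutes-adjusted model. The cost is some protocol wording, three named contrasts and a descriptive table. The downside is a narrower claim than optimal timing.
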